## Data and safety monitoring plan

An independent data safety monitoring board (DSMB) will be established consisting of at least 5 independent experts in malaria control, diagnosis, case management, biostatistics and epidemiology and one member of the research team who will receive monthly reports of adverse events during the intervention period of the trial. The charter will include trial stopping rules for safety. No data on futility or benefit will be determinable during the course of the trial as seasonality of malaria transmission timing of outcome data collection preclude developing stopping rules based on outcome data collected during the duration of the implementation of the intervention. Safety concerns associated with the wide scale use of DHAP, although unexpected, will form the basis of development of a stopping rule. The stopping rules for this trial will be based on detection of a significantly higher rate of mortality, hospitalization for possible drug related events, or any other severe adverse event in the RFDA intervention arm compared to expected rates in the control group.

In addition to the DSMB, a regional monitor will be used for supervision of study progress and adverse events. A study pharmacist from the provincial health office will also be used to manage and account for the supply of DHAP used in the study.

## Potential benefits of the proposed research to the participants and others

The selected areas as a whole and the children within the selected areas specifically will benefit from reductions in the burden of malaria disease as a result of the decreased reservoir of asymptomatic parasitemia. The development of novel strategies to further reduce malaria transmission beyond the capacity of insecticide treated nets and case management is essential to proceed toward malaria elimination.

RFDA provides additional benefit beyond the standard RFTAT intervention through the treatment of subpatent asymptomatic malaria infections and the provision of chemoprophylaxis in areas with recent malaria transmission.

## Collection of specimens

Each specimen upon collection will be given a unique id that contains no personally identifiable information. Participants data linked to this identification number will only be accessed by the principal investigators or with permission from the principal investigator. Data stored on paper will be stored in a locked room. Data stored electronically will be saved to a password-protected computer.

## Protocol Accessibility

The complete protocol will be registered at clinicaltrials.gov, ahead of intervention delivery in the study site. This will prevent the likelihood of undeclared post-hoc changes to the protocol following IRB submission and of selective outcome reporting when the trial results are published. Additionally, this will provide peers and relevant partners working in the arena of malaria control and elimination, advanced warning of a trial being planned for to prevent duplication of efforts where the outcomes of this trial may hold external validity for their given malaria transmission setting.

# Timeline

|  | **Year 1** | | | | | | | | | | | | **Year 2** | | | | | | | | | | | | **Year 3** | | | | | | |
| --- | --- | --- | --- | --- | --- | --- | --- | --- | --- | --- | --- | --- | --- | --- | --- | --- | --- | --- | --- | --- | --- | --- | --- | --- | --- | --- | --- | --- | --- | --- | --- |
| **Activity/Month** | **1** | **2** | **3** | **4** | **5** | **6** | **7** | **8** | **9** | **10** | **11** | **12** | **1** | **2** | **3** | **4** | **5** | **6** | **7** | **8** | **9** | **10** | **11** | **12** | **1** | **2** | **3** | **4** | **5** | **6** | **7** |
| Submission to IRB |  |  |  |  |  |  |  |  |  |  |  |  |  |  |  |  |  |  |  |  |  |  |  |  |  |  |  |  |  |  |  |
| Recruitment and training of program staff |  |  |  |  |  |  |  |  |  |  |  |  |  |  |  |  |  |  |  |  |  |  |  |  |  |  |  |  |  |  |  |
| Sensitization of communities / chiefs / district personnel |  |  |  |  |  |  |  |  |  |  |  |  |  |  |  |  |  |  |  |  |  |  |  |  |  |  |  |  |  |  |  |
| Recruitment and training of CHWs, Health center staff and district personnel |  |  |  |  |  |  |  |  |  |  |  |  |  |  |  |  |  |  |  |  |  |  |  |  |  |  |  |  |  |  |  |
| Recruitment and training of survey teams |  |  |  |  |  |  |  |  |  |  |  |  |  |  |  |  |  |  |  |  |  |  |  |  |  |  |  |  |  |  |  |
| Consent process of research areas |  |  |  |  |  |  |  |  |  |  |  |  |  |  |  |  |  |  |  |  |  |  |  |  |  |  |  |  |  |  |  |
| Collection of cohort data / samples in research areas |  |  |  |  |  |  |  |  |  |  |  |  |  |  |  |  |  |  |  |  |  |  |  |  |  |  |  |  |  |  |  |
| Lab analysis of samples (DNA / Ab) |  |  |  |  |  |  |  |  |  |  |  |  |  |  |  |  |  |  |  |  |  |  |  |  |  |  |  |  |  |  |  |
| Endline survey |  |  |  |  |  |  |  |  |  |  |  |  |  |  |  |  |  |  |  |  |  |  |  |  |  |  |  |  |  |  |  |
| PCR analysis of endline survey samples |  |  |  |  |  |  |  |  |  |  |  |  |  |  |  |  |  |  |  |  |  |  |  |  |  |  |  |  |  |  |  |
| Endline Survey data process and cleaning |  |  |  |  |  |  |  |  |  |  |  |  |  |  |  |  |  |  |  |  |  |  |  |  |  |  |  |  |  |  |  |
| Evaluation analysis |  |  |  |  |  |  |  |  |  |  |  |  |  |  |  |  |  |  |  |  |  |  |  |  |  |  |  |  |  |  |  |
| Final dissemination of results |  |  |  |  |  |  |  |  |  |  |  |  |  |  |  |  |  |  |  |  |  |  |  |  |  |  |  |  |  |  |  |

# Appendices

Appendix 1 Step D Protocol: Current RFTAT intervention in Southern Province v1

Appendix 2 Active Infection Detection Protocol: Current RFTAT intervention in Lusaka v1

Appendix 3 Consent and Information Sheet for Household Survey: Endline surveys v4

Appendix 4 MIS Questionnaire for Parasite Evaluation: Endline survey questionnaire v2

Appendix 5 Oral Assent for Children 6-17 years for DHAP administration v2

Appendix 6 RFTAT Questionnaire: Research responses v2

Appendix 7 RFDA Questionnaire: Research responses v2

Appendix 8 Longitudinal Study Consent Form: Research responses on days 0, 3, 30 and 90 v3

Appendix 9 3-day post Questionnaire: Research responses v2

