## Reactive responses

All reactive responses will aim to take place within 7 days following presentation of an RDT positive incident malaria case to a health center or health post within the study areas. Based on work showing the spatial distribution of malaria infections in Southern Province ([name] dissertation, unpublished), all individuals residing within 140 meters of the index case household will be included in the reactive response. In the control (RFTAT) arm, the current standard of care will be provided in which individuals will be tested for malaria using an RDT. Positive individuals will be offered treatment with AL or referred to a health center according to national treatment guidelines. In the intervention (RFDA) arm, all individuals residing within 140 meters of the index case household will be offered DHAP. Testing with an RDT will not be performed in the RFDA arm, with the exception of research team responses (see Section 2.4.1 on page 20).

[figure not shown]

Figure 6 - Schematic of activities before and during a CHW reactive response. HC, Health Center; HP, Health Post; AL, artemether-lumefantrine. Seated / standing figures indicate individuals who are symptomatic or healthy respectively. The colour of individuals represents whether they are infected with P. falciparum (Red) or uninfected (black).

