## Consent

Written informed consent will be sought for each interaction. A summary of consent procedures is shown in Table 2. In the event that an individual refuses DHAP, the individual will be offered the standard of care in Zambia, which currently consists of RFTAT with an RDT and AL. To monitor refusal rates, the number of people who opt-out will be recorded.

Table 2 – Consent schedule and timing of data collection.

|  | Written informed consent for intervention | Written informed consent for DBS (finger stick) | Written informed consent for data collection |
| --- | --- | --- | --- |
| Endline Survey |  | X  (Appendix 3) | X  (Appendix 3) |
| Passive Case Detection |  |  |  |
| RFTAT intervention* |  |  |  |
| RFDA intervention | X  (Appendix 11) |  |  |
| Reactive Research Response (RFTAT / RFDA) | X  (Appendix 11 – RFDA Only) | X  (Appendix 8⁺) | X  (Appendix 8⁺) |
| - 3 day follow-up |  |  | X  (Appendix 8⁺) |
| - 30 day follow-up |  | X  (Appendix 8⁺) | X  (Appendix 8⁺) |
| - 90 day follow-up |  | X  (Appendix 8⁺) | X  (Appendix 8⁺) |

*Current routine strategy

⁺Individuals will be consented at the first visit for all subsequent interactions.

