## Adequacy of protection against risks

We will administer an informed written consent and assent form in English or the local language as required by the participant. Table 4 outlines the exclusion criteria, inclusion ages and consent / assent forms that will be administered. For the household survey, written consent for participation in the survey and intervention will be provided by an individual who is at least 18 years of age according to the laws of Zambia. These forms will be read and explained or will be given to participants to read themselves and will include a full description of voluntary participation, the right to withdraw from the study at any time and the right to not answer any question. The forms will also address the risks, benefits and purpose of the intervention and study, including what we hope to learn. For individual’s ≥1 month and less than 18 years of age, consent will be sought from the head of household or parent/household guardian above age 18. For children greater than six years and less than 18, oral assent will be sought from the child. We will train all interviewers extensively on the consent and assent procedures. Checks in the field by the project team, including observation of a reactive response, assessment of completed consent statements and questioning of the interviewer will ensure the consent process is strictly followed. The confidentiality procedures (listed in section 2.11 on p33) are designed to meet all contingencies so that the privacy of the participants is preserved.

| **Study/intervention data collection** | **Exclusion** | **Inclusion Ages** | **Consent/Assent** |
| --- | --- | --- | --- |
| **Endline Survey** | < 1 month or >15 years of age | ≥1 month and <6 years old | Adult Consent (Appendix 3) |
|  |  | 6-<15 years old | Oral assent (Appendix 19) |
| **RFTAT intervention** | Severe malaria patients, First trimester pregnant women, < 1 month of age | ≥3 months old | DHAP Consent (Appendix 11) |
| **RFDA intervention** | Severe malaria patients, First trimester pregnant women, < 3 months of age, individuals contraindicated for DHAP | ≥3 months old  ≥1 month old | Oral Assent 6-17 years (Appendix 16) |
|  |  |  | Reactive research response (Appendix 8) |
| **Research around reactive responses for RFTAT and RFDA** | < 1 month of age | ≥1 month old | Oral Assent 6-17 years (Appendix 16 |
|  |  |  |  |

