Table 4 - Summary of inclusion / exclusion criteria and consent/assent forms. * RFTAT with AL represents current standard of care so consent / assent will not be required.

The development of drug resistance has been linked to the administration of therapeutic doses of antimalarials

^11^. Our proposed strategy to reduce the risk of the development of drug resistance includes:

- Directly observed treatment of the first dose of DHAP during all reactive responses
- In research responses, the team will additionally:
  - Check blister packs on day 3 to ensure that the second dose was taken
  - Directly observed treatment of the third dose of DHAP on day 3

Our proposed strategy to reduce risks associated with finger sticks includes:

- To clearly explain the procedures to each individual or caretaker so that they understand the transient pain associated with collection of finger prick blood samples and the extremely low risk of infection.
- To use specially trained and supervised fieldworkers who will be able to answer commonly asked questions.
- To specially train fieldworkers to collect and handle biological specimens and ensure that all data entry personnel are trained on confidentiality and safety issues, as well as on informed consent procedures. This includes special training for all team members on universal precautions for handling biological specimens.

DHAP has been approved by the Zambian Ministry of Health as the new alternate first-line standard of care drug for the treatment of uncomplicated malaria in Zambia. AL is also the first-line treatment for uncomplicated malaria and is widely available. A new Cochrane Review (2014) has shown that studies comparing DHAP to other antimalarials to be safe, effective and well-tolerated by individuals

^47^. DHAP is a combination of two antimalarial drugs (dihydroartemesinin and piperaquine). Dihydroartemesinin has been associated with the following: prolonged QT intervals, falciparum malaria, influenza, cough, fever, abnormal cardiac conduction, necrotizing enterocolitis in foetus or new-borns, leukocytosis, neutropenia, thrombocytopenia, hepatitis and seizure. The risk of DHAP is assumed similar to that of AL, the current widely available national first line treatment for uncomplicated malaria.

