Appendix 10 30-day and 90-day post Questionnaire: Research responses v2

Appendix 11 Consent and information sheet for administration of DHAP (RFDA Arm only) v6

Appendix 12 Routine Step B and Step D Data elements collected v1

Appendix 13 Adverse event reporting form v2

Appendix 14 Adverse event investigation form v2

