Appendix 15 Register of recording adverse events v1

Appendix 16 Oral Assent for Children 6-17 years for malaria blood test v2

Appendix 17 CHW register for RFTAT v1

Appendix 18 CHW register for RFDA v1

Appendix 19 Oral Assent for Children 6-15 years for malaria survey

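### Table 4 cites the blood-test assent (Appendix 16) for children aged 6-17 in the RFDA intervention, where the DHAP assent (Appendix 5) belongs by its title

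*Protocol*

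**What the plan says.** Section 3.1 (Adequacy of protection against risks) commits to oral assent from children between six and 18, in addition to consent from a parent, guardian or household head. It says the forms will explain the risks, benefits and purpose of both the intervention and the study. It then refers to Table 4 for the forms to be used.

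For the reactive responses, Table 4 lists four entries in this order:

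1. the DHAP consent, "DHAP Consent (Appendix 11";
2. an assent, "Oral Assent 6-17 years (Appendix 16";
3. the research-response consent (Appendix 8);
4. the same assent again (Appendix 16).

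Section 6 (Appendices) gives the titles:

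- "Appendix 5 Oral Assent for Children 6-17 years for DHAP administration v2"
- "Appendix 11 Consent and information sheet for administration of DHAP (RFDA Arm only) v6"
- "Appendix 16 Oral Assent for Children 6-17 years for malaria blood test v2"

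On testing, Section 2.4 (Reactive responses) states: "Testing with an RDT will not be performed in the RFDA arm, with the exception of research team responses". The Definitions of Key Terminology say that most responses in either arm are carried out by one community health worker (CHW) alone.

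**The concern.** The protocol has written an assent form for the drug and another for the blood test, but its assignment table uses only the second. In a CHW-led RFDA response the child is offered DHAP and has no routine blood test, so the form that Table 4 names does not match what is done. In an RFDA research response it covers the finger prick but, by its title, not the drug.

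At stake is whether minors are asked about the treatment they are offered, as Section 3.1 promises. Field teams and CHWs are likely to be trained from the table, so a wrong form number there could become a repeated consent deviation.

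**Working it through.** The plan has no design figure to reproduce here. The check sets the tables against the appendix list.

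**Step 1. Where assent forms are assigned.** Table 2 in Section 2.7 lists written consent only. Table 4 is the only place that links an assent form to an activity.

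**Step 2. Does each consent sit with an assent for the same activity?** Judged by titles:

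| Consent in Table 4 | Assent that follows it | Same activity? |
| --- | --- | --- |
| Appendix 3, household survey | Appendix 19, malaria survey | Yes |
| Appendix 11, DHAP administration | Appendix 16, malaria blood test | No |
| Appendix 8, research responses | Appendix 16, malaria blood test | Yes, for the finger prick |

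Only the DHAP pair fails, and Appendix 5 is the form whose title would complete it.

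**Step 3. Could displaced table rows explain it?** In the text as read, the DHAP consent stands against the RFTAT row. That cannot be the intended place: Appendix 11 is titled for the RFDA arm only, and the note to Table 4 says "RFTAT with AL represents current standard of care so consent / assent will not be required". The DHAP consent and the assent after it therefore belong to RFDA. Any realignment only moves entries that are already in the table, and Appendix 5 is not among them.

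**Step 4. Is Appendix 5 cited elsewhere?** In the text at hand it appears only in the appendix list.

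**Step 5. How often is there no blood test?** Section 2.4 excludes RDTs in the RFDA arm outside research responses, and Section 2.4.1 describes dried blood spots for research responses. The Project summary gives about 30,000 people in reactive responses and about 9,000 in the subset studied for re-infection, importation and serology. The share outside that subset is

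1 − 9,000/30,000 = 0.70, or about 70%.

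This covers both arms and all ages. Applying it to RFDA children aged 6-17 assumes the same proportion in that arm and age band. It agrees with the statement that CHW-only responses are the majority.

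**Step 6. Exceptions.** Some RFDA participants outside research responses may have an RDT: women of reproductive age (12-49) with a first-trimester, test-detected or uncertain pregnancy (Treatment notes under Section 2.2.2), and people who refuse DHAP and are offered the standard of care (Section 2.7). The accurate wording is therefore no routine blood test, not no blood test at all.

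**The case against.** The strongest reply is that this is a slip in a cross-reference and nothing more. The DHAP assent exists and has reached version 2, Section 3.1 promises child assent with forms that address the intervention, and guardian consent to DHAP is required in any case. Being uncited is also weak evidence of being unused: Appendices 15, 17 and 18 are not cited in the body either. The texts of the forms are not shown, so their content is known only from their titles. All of this stands, and it makes a wrong appendix number the likeliest explanation. It does not remove the error, because the one table that assigns assent forms puts a different form in the place of the DHAP assent.

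Three stronger readings are tempting, and the documents do not support them.

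- A reader might infer that children are not asked about the drug. No passage says so, and Section 3.1 points the other way.
- A reader might infer that the refusal count would record blood-test refusals, or that RFDA coverage, an effect modifier in Secondary Aims 2 and 8, would be misread. Section 2.7 introduces the count with refusal of DHAP and then says "To monitor refusal rates, the number of people who opt-out will be recorded"; nothing derives it from assent forms. Coverage is not defined by assent forms either, and a wrong form number does not change who received the drug.
- A reader might put a number on the children left unasked. That would need an age split the protocol does not give, an even split between arms, and the unproven premise that no DHAP assent is sought.

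**Conclusion.** The point holds as an internal inconsistency in an operative participant-protection table. Taken literally, Table 4 assigns the wrong assent form to every child aged 6-17 in the RFDA intervention, and for most of them the form names a procedure they would not routinely undergo. This conflicts with the commitment in Section 3.1. It should be corrected before the table is used for training or in the field.

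The conclusion rests on the form titles, since the forms themselves are not shown, and on reading the DHAP consent and the assent after it as belonging to RFDA, which the title of Appendix 11 and the note to Table 4 both support. There is no statistical consequence: no outcome, estimate or analysis is shown to be affected.

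**What to change.** In Table 4:

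- cite Appendix 5 for the RFDA intervention at ages 6-17, in both CHW-led and research responses;
- keep Appendix 16 for research responses, where study blood is taken; in the RFDA arm it is used in addition to Appendix 5;
- realign the rows so that the RFTAT row carries no DHAP consent, in line with the table's own note.

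CHW and team instructions should be checked against the corrected table. The DHAP assent already exists, so no new document is needed. The cost is an edit to one table, plus one more short assent form for RFDA children in research responses.

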Appendix 10 30-day and 90-day post Questionnaire: Research responses v2

Appendix 11 Consent and information sheet for administration of DHAP (RFDA Arm only) v6

Appendix 12 Routine Step B and Step D Data elements collected v1

Appendix 13 Adverse event reporting form v2

Appendix 14 Adverse event investigation form v2

Appendix 15 Register of recording adverse events v1

Appendix 16 Oral Assent for Children 6-17 years for malaria blood test v2

Appendix 17 CHW register for RFTAT v1

Appendix 18 CHW register for RFDA v1

Appendix 19 Oral Assent for Children 6-15 years for malaria survey
